### Causality

**Not related or improbable**: a clinical event including laboratory test abnormality with temporal relationship to trial intervention administration which makes a causal relationship incompatible or for which other treatments, chemicals or disease provide a plausible explanation**.** This will be counted as “unrelated” for notification purposes.

**Possible**: a clinical event, including laboratory test abnormality, with temporal relationship to trial intervention administration which makes a causal relationship a reasonable possibility, but which could also be explained by other interventions, chemicals or concurrent disease. This will be counted as “related” for notification purposes.

**Probable**: a clinical event, including laboratory test abnormality, with temporal relationship to trial intervention administration which makes a causal relationship a reasonable possibility, and is unlikely to be due to other interventions, chemicals or concurrent disease. This will be counted as “related” for notification purposes.

**Definite**: a clinical event, including laboratory test abnormality, with temporal relationship to trial intervention administration which makes a causal relationship a reasonable possibility, and which can definitely not be attributed to other causes. This will be counted as “related” for notification purposes.

With regard to the criteria above, medical and scientific judgment shall be used in deciding whether prompt reporting is appropriate in that situation.

### Reporting of adverse events

Participants will be asked to contact the study site immediately in the event of any serious adverse event. All adverse events will be recorded and closely monitored until resolution, stabilisation, or until it has been shown that the study intervention is not the cause. The Chief Investigator shall be informed immediately of any serious adverse events and shall determine seriousness and causality in conjunction with any treating medical practitioners.

##

## Trial Intervention Related SAEs

**A serious adverse event that is unexpected in its severity and seriousness *and* deemed directly related to or suspected to be related to the trial intervention shall be reported to the ethics committee that gave a favourable opinion as stated below.**

**The event shall be reported immediately of knowledge of its occurrence to the Chief Investigator.**

**The Chief Investigator will:**

- Assess the event for seriousness, expectedness and relatedness to the trial treatment or intervention.
- Take appropriate medical action, which may include halting the trial and inform the Sponsor of such action.
- If the event is deemed related to the trial intervention shall inform the REC using the reporting form found on the NRES web page within 7 days of knowledge of the event.
- Shall, within a further eight days send any follow-up information and reports to the REC.
- Make any amendments as required to the study protocol and inform the REC as required

### Participant removal from the study due to adverse events

Any participant who experiences an adverse event may be withdrawn from the study at the discretion of the Investigator.

# ETHICAL AND REGULATORY ASPECTS

## ETHICS COMMITTEE AND REGULATORY APPROVALS

The trial will not be initiated before the protocol, informed consent forms and participant and GP information sheets have received approval / favourable opinion from the Research Ethics Committee (REC), the respective National Health Service (NHS) or other healthcare provider’s Research & Development (R&D) department, and the Health Research Authority (HRA) if required. Should a protocol amendment be made that requires REC approval, the changes in the protocol will not be instituted until the amendment and revised informed consent forms and participant information sheets have been reviewed and received approval / favourable opinion from the REC and R&D departments. A protocol amendment intended to eliminate an apparent immediate hazard to participants may be implemented immediately providing that the REC are notified as soon as possible, and an approval is requested. Minor protocol amendments only for logistical or administrative changes may be implemented immediately; and the REC will be informed.

The trial will be conducted in accordance with the ethical principles that have their origin in the Declaration of Helsinki, 1996; the principles of Good Clinical Practice, and the UK Department of Health Policy Framework for Health and Social Care, 2017.

## INFORMED CONSENT AND PARTICIPANT INFORMATION

The process for obtaining participant informed consent will be in accordance with the REC guidance, and Good Clinical Practice (GCP) and any other regulatory requirements that might be introduced. The investigator or their nominee and the participant shall both sign and date the Informed Consent Form before the person can participate in the study.

The participant will receive a copy of the signed and dated forms and the original will be retained in the Trial Master File. A second copy will be filed in the participant’s medical notes and a signed and dated note made in the notes that informed consent was obtained for the trial.

The decision regarding participation in the study is entirely voluntary. The investigator or their nominee shall emphasize to them that consent regarding study participation may be withdrawn at any time without penalty or affecting the quality or quantity of their future medical care, or loss of benefits to which the participant is otherwise entitled. No trial-specific interventions will be done before informed consent has been obtained.

The investigator will inform the participant of any relevant information that becomes available during the course of the study, and will discuss with them, whether they wish to continue with the study. If applicable they will be asked to sign revised consent forms.

If the Informed Consent Form is amended during the study, the investigator shall follow all applicable regulatory requirements pertaining to approval of the amended Informed Consent Form by the REC and use of the amended form (including for ongoing participants).

## RECORDS

### Case Report Forms

Each participant will be assigned a trial identity code number, allocated at randomisation if appropriate, for use on CRFs other trial documents and the electronic database. The documents and database will also use their initials (of first and last names separated by a hyphen or a middle name initial when available) and date of birth (dd/mm/yy).

CRFs will be electronic using REDCap secure system and will include participants anthropometric measurements, participants demographics and health/medication history, and FibroScan™ and MRI (if applicable) results.

CRFs will be treated as confidential documents and held securely in accordance with regulations. The investigator will make a separate confidential record of the participant’s name, date of birth, local hospital number or NHS number, and Participant Trial Number (the Trial Recruitment Log), to permit identification of all participants enrolled in the trial, in accordance with regulatory requirements and for follow-up as required.

CRFs shall be restricted to those personnel approved by the Chief or local Principal Investigator and recorded on the ‘Trial Delegation Log.’

All paper forms shall be filled in using black ballpoint pen. Errors shall be lined out but not obliterated by using correction fluid and the correction inserted, initialled and dated.

The Chief or local Principal Investigator shall sign a declaration ensuring accuracy of data recorded in the CRF.

With personnel who are qualified by education, training, and experience to perform their respective tasks and that the study will not use the services of study personnel for whom sanctions have been invoked or where there has been scientific misconduct or fraud.

Trial related information such as case report forms and other biochemical data will be stored in study files and updated to an electronic data base (Microsoft excel) to facilitate analyses. Electronic forms will be stored on UoN shared drives.

MRI data will be downloaded from the 3T UoN MRI machines and stored on UoN shared drives.

### Sample Labelling

Each participant will be assigned a trial identity code number for use on the samples, consent forms and other study documents and the electronic database. The documents and database will also use their initials (of first and last names separated by a hyphen or a middle name initial when available) and date of birth (dd/mm/yy).

Samples for NHS pathology analysis will be labelled in accordance with local NHS procedures.

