## RANDOMIZATION AND BLINDING

The study will be a parallel design, placebo controlled, randomised intervention study in which participants will be allocated to either the intervention or placebo arm. The randomisation will be done through an online software (sealedenvelope.com) to determine intervention A or B at enrolment.

One of research team will be un-blinded and will be responsible for preparing and labelling of the intervention/placebo as either A or B based on random selection using an online software (sealedenvelope.com). A or B – pectin will be assigned to the arm in the first envelope. This information will be securely documented in a new sealed enveloped stored in the chief investigators locked desk. All other members of the team will be blinded to the assignment of A or B as the intervention.

This will be unblinded once the study is complete after the sample analysis and data analysis is complete.

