## TRIAL/STUDY MANAGEMENT

The CI has overall responsibility for the study and shall oversee all study management.

The data custodian will be the Chief Investigator.

The study will form part of PhD project undertaken by [name] registered at the University of Nottingham (UoN) whose role will include responsibility for recruiting and consenting patients and collecting data. The PhD student will be responsible for arranging and conducting study visits, analysing samples and analysing the data. The student will comply with University of Nottingham policies and regulations.

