**Dietary intervention (6 weeks):**

Control and intervention arms: Each participant will be randomly assigned to either pectin with whey protein and cocoa powder or control whey protein with cocoa powder using online software (sealedenvelope.com) to determine intervention A or B at enrolment. Randomisation will ensure equal distribution of key characteristics that might confound between-group comparisons and will be evaluated using baseline data analysis. Participants in the intervention arm (N=15) will be required to take 15g of pectin combined with 15g of unflavoured whey protein powder and 5g of cocoa powder as a flavour per day for a period of 6 weeks. The participants in the placebo/control arm (N=15) will be required to take 30g of unflavoured whey protein powder combined with 5g of cocoa powder as a flavour per day for the same period of 6 weeks. All supplements will be provided, pre-weighed, in food grade pouches and will be given sufficient cover the total intake for the 6-weeks period. Participants will be asked to incorporate the supplement provided in 250-300ml of water taken once at morning or evening. Regular weekly contact will be made via phone calls by [name] to record patients’ feedback or any adverse event that might occur due to ingestion of supplements and to ensure participants receive any information that becomes available during the course of the research that may be relevant to their continued participation .

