## TRANSPORT AND STORAGE OF THE TISSUES

Samples will be stored in a linked anonymised format and labelled using a combination of study reference, unique study identifier and cross referenced with location code numbers to permit accurate linkage to study data and the consent form. Where participant’s consent, samples will be collected for analysis of common genetic variants associated with development of gut permeability [15].

Stool samples will be collected and stored in aliquots at -80°C.

Blood samples will be collected and either sent for clinical analyses or stored or processed to obtain plasma and serum aliquots which will be stored at -80°C. They will be transported within the building from the patient to the lab in double containment with absorbent material and following Biosafety requirements.

The master sample database will be held by the research team in a password encrypted file.

The analysis of samples will take place at the University of Nottingham within the School of Medicine located in the Queens Medical Centre, or at Nottingham University Hospitals NHS Trust, Queens Medical Centre clinical laboratories or at contracted commercial service providers.

Samples will be transferred by an approved courier for analysis by external agents at the end of the study. All shipments will contain a complete inventory of all samples, along with the name of the person responsible for sending the samples. Any remaining samples at the University of Nottingham will be stored either under the University HTA Licence (DI [name]- Licence Number 12265) or within a Research Tissue Bank for future research if participants are agreeable and sign the optional clause on the consent form.

Where participants do not agree to the future use of the samples they will be destroyed after the study ends in accordance with the Human Tissue Act, 2004.

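### Masking of the primary assays is stated but weakly protected: one participant ID links each tube to a person whose likely arm the in-house operator could infer.

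*Protocol*

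**What the plan says.** **Labelling.** Under Records, Sample Labelling, each participant receives "a trial identity code number for use on the samples, consent forms and other study documents and the electronic database". The same section adds that "The documents and database will also use their initials" and date of birth; it does not say that these go on the tubes. Transport and Storage of the Tissues says "Samples will be stored in a linked anonymised format and labelled using a combination of study reference, unique study identifier", with cross-reference to location codes. Neither section mentions an arm letter or a visit code on the tube. Neither gives research aliquots a laboratory code separate from the participant ID.

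**Who does what.** Trial/Study Management gives the PhD student "responsibility for recruiting and consenting patients and collecting data", and continues: "The PhD student will be responsible for arranging and conducting study visits, analysing samples and analysing the data". Laboratory Analyses has the blood markers measured either by the research laboratory team with commercial kits or by contracted commercial laboratories.

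**Masking.** Randomization and Blinding keeps everyone except one team member blind to whether A or B is pectin. On timing it says: "This will be unblinded once the study is complete after the sample analysis and data analysis is complete". The next section puts the code in a sealed envelope in the chief investigator's desk.

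**The letter.** Packaging and labelling marks each bag with the arm letter only. The Synopsis (Description of interventions) and Trial/Study Configuration both identify A as the pectin or intervention arm and B as placebo.

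**Participant feedback.** The section on the six-week dietary intervention has one named person (name removed) telephone participants weekly to record feedback and adverse events. Known Side Effects names bloating as a possible effect of added fibre.

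**The concern.** Seven blood markers make up the primary endpoint, so the assay bench is where the primary outcome is created. Bench work can involve judgement: whether to re-run a well, accept a replicate or set aside an implausible value. If the operator can tell whose sample it is and has a good idea of that person's arm, those decisions can lean towards the expected direction of change. Once values have been selected in this way, no later analysis can reliably detect or undo it. With 15 participants per arm, one or two such decisions are enough to matter.

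The protocol clearly intends to prevent this, because it holds the code until sample analysis is over. The question is whether the labelling, the allocation of duties and the handling of the arm letter support that intention.

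**Working it through.** **Step 1. From tube to person.** The sample and the consent form share one ID (Sample Labelling). The person assigned to consent and visits is also assigned sample analysis (Trial/Study Management). If that person runs an assay in-house, the tube label is enough to identify the participant.

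**Step 2. From person to likely arm.** The ID alone does not give the arm. Two other routes could.
- *The letter.* Bags are marked A or B and are handed out at the baseline visit. The student conducts study visits, so would be expected to see them. The sealed code is meant to hide which letter is pectin, but the Synopsis and Trial/Study Configuration both print A as pectin or intervention. Either those sections disclose the code, or they conflict with a code that was to be set at random.
- *Feedback.* Reports of bloating would suggest fibre rather than whey alone. That the weekly caller is the student is an inference from the list of duties, because the name is removed.

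**Step 3. What the documents leave open.** No section puts the visit on the tube. Baseline and week-6 samples under one ID must be told apart somehow, but the means is not given. Nor is it stated that the student assays every primary marker, since commercial laboratories are also allowed.

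**Step 4. How much selective rejection could matter.** The plan gives no figure to reproduce, so this is a what-if. Assumptions: no true effect, 15 per arm (from the protocol), normal week-6 values, unadjusted independent t-test at two-sided 5%, a marker where lower favours pectin, 200,000 simulated trials.

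The shift in the pectin mean can be checked by hand. The expected largest and second-largest of 15 standard normal values are 1.736 and 1.248.
- Drop one: −1.736 / 14 = −0.124 SD.
- Drop two: −(1.736 + 1.248) / 13 = −2.984 / 13 = −0.230 SD.

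| Rejection rule | Shift in pectin mean | p < 0.05, two-sided | Of which favouring pectin |
|---|---|---|---|
| None | 0 | 5.0% | 2.5% |
| Highest pectin value | −0.12 SD | 7.1% | 5.8% |
| Two highest pectin values | −0.23 SD | 10.8% | 10.0% |
| Highest of all 30, arm ignored | not applicable | about 5.0% | about 2.5% |

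Repeat runs differ by about 0.1 percentage point. For a marker expected to rise, such as IL-10, the same figures apply to dropping the lowest values, because the normal distribution is symmetric.

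**Step 5. Reading the table.** All the inflation is in the two rows where the operator knows the arm. Knowing only whose tube it is, with no clue to arm, does not bias the between-arm comparison. The shared ID matters because it carries knowledge of the likely arm to the bench.

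**The case against.** The strongest reply is that the assays are masked. Randomization and Blinding says so, and a participant ID is not an arm code. This stands as far as it goes: a reader might infer from the shared ID that the primary assays are unmasked, and the protocol does not support that. It states arm masking through sample analysis. What it lacks is protection of that masking at the bench, and two of its own sections print the letter's meaning.

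A reader might also infer that the operator sees which visit a tube comes from, or that initials and date of birth are on the tube. Neither is stated. Nor is it certain who runs the assays: a commercial laboratory that has never met the participants would largely remove the problem for the markers it measures. The concern is therefore limited to assays run in-house.

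The description "Samples will be stored in a linked anonymised format" is not contradicted by a shared ID, since linkage is what the term means. Rules for re-runs and outliers commonly belong in a laboratory manual or statistical analysis plan, so their absence is not counted here. Initials and date of birth in the database are a separate data-protection matter.

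The simulation is open to fair criticism. It uses an unadjusted test on week-6 values, whereas the Methods section plans mixed models adjusted for baseline and covariates. It also assumes normal data and rejection in every trial. It shows only that one or two choices can matter at this sample size; it does not predict this trial's error rate.

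Finally, it can be argued that the printed letter is the real weakness and the tube label secondary. That is partly right, and correcting the label alone would leave the letter decoded in the protocol. Correcting the letter alone would still leave participant feedback as a clue, which a separate tube code blocks at the bench.

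**Conclusion.** The point holds in a limited form. Arm masking of the primary assays is promised but poorly protected. One ID runs from consent form to tube, the person who sees participants may also analyse samples, bags carry the arm letter, and the protocol prints A as pectin while treating the code as sealed. For in-house assays, the operator could link a tube to a participant and a likely arm.

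The possible size is a false-positive rate of about 7.1% or 10.8% instead of 5%, nearly all of the excess favouring pectin. This assumes that the operator knows the arm and selectively rejects one or two values out of 15. If rejection is blind to arm the rate stays at about 5%, and with no rejection there is no bias. How often selective rejection would occur cannot be read from the protocol. The change is worth making before samples are assayed, because the remedy is cheap and the bias cannot be repaired afterwards.

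**What to change.** 1. In Sample Labelling, state that research aliquots carry a random laboratory code unrelated to participant ID, visit or arm. NHS pathology samples can keep their local labelling.
2. Have the key held by the team member who is already unblinded or by the trial statistician, provided that person does not run the assays.
3. Merge results to participant and visit only after assay values, re-runs and exclusions are locked.
4. Reconcile the Synopsis, Trial/Study Configuration and Packaging and labelling with the two sections on the sealed code, so that the letter on a bag does not reveal the arm.

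The cost is a code list, printed labels and a few sentences of protocol text, with no extra staff. The downsides are a merge step, the need to safeguard the key, and that the key holder must arrange the plate layout because the operator no longer can.

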### Source documents

Source documents shall be filed at the investigator’s site and may include but are not limited to, consent forms, current medical records, laboratory results and records. A CRF may also completely serve as its own source data. Only trial staff as listed on the Delegation Log shall have access to trial documentation other than the regulatory requirements listed below.

### Direct access to source data / documents

The CRF and all source documents, including progress notes and copies of laboratory and medical test results shall made be available at all times for review by the Chief Investigator, Sponsor’s designee and inspection by relevant regulatory authorities (e.g. DH, Human Tissue Authority).

## DATA PROTECTION

All trial staff and investigators will endeavour to protect the rights of the trial’s participants to privacy and informed consent, and will adhere to the Data Protection Act, 2018. The CRF will only collect the minimum required information for the purposes of the trial. Access to the information will be limited to the trial staff and investigators and relevant regulatory authorities (see above). Computer held data including the trial database will be held securely and password protected. All data will be stored on a secure dedicated web server. Access will be restricted by user identifiers and passwords (encrypted using a one-way encryption method).

Information about the trial in the participant’s medical records / hospital notes will be treated confidentially in the same way as all other confidential medical information.

Electronic data will be backed up every 24 hours to both local and remote media in encrypted format.

